**Analysis Plan**

We will calculate descriptive statistics (mean, standard deviation, quartiles) and construct graphs (histograms, scatter plots, box-plots) to characterize the clients at baseline with respect to socio-demographic factors, housing status, health status, and health service use. Baseline group comparisons will be conducted using chi-square test or Fisher’s exact test (for categorical variables), t-test or Wilcoxon rank-sum test (for continuous variables). We will construct plots to describe longitudinal changes in primary and secondary outcomes over time. All analyses will use an intent-to-treat perspective and will be compared with a per-protocol analysis. The primary outcome evaluates the proportional change in rate of emergency department visits (ED visits) between pre-intervention and 6-month time intervals post-intervention; some secondary outcomes (number of hospitalizations, days in hospital) are also count measures, negative binomial outcomes will be compared with Poisson regression accounting for overdispersion to determine the overall treatment effect. While it is usually customary to match the sample size calculation technique to analysis approach, in this case insufficient published data is available to calculate a sample size for a marginal techniques (Generalized Estimating Equations - GEE) that is proposed as our primary analytic technique. While GEE models represent the main question being studied (the impact of the intervention on population measures of ED use), conditional models can also provide useful information and sample size techniques require fewer assumptions. For this reason, both marginal and conditional (random effects models) will be fit and compared during the data analysis phase of this study. The choice of the most appropriate representation of the overdispersion of data (Negative binomial versus the use of an overdispersion factor in a poisson regression) is highly dependent on the variance structure observed in the collected data (Ver Hoef & Boveng, 2007); hence, the covariance estimates of the observed data will inform final model selection. GEE and mixed effects models will be compared to account for the repeated measurement of participants. A literature review and the presence of clinically significant differences in baseline data will determine which, if any, covariates require adjustment in the final model, and these will be included as covariates in the generalized linear regression models. Other secondary normally distributed outcomes (quality of life, service satisfaction) with be analysed using linear regression using the same principles of adjustment for clinically important covariates, and marginal versus conditional approaches.

Given the possibility of missing data in following participants for 12 months who may have unstable housing or community connections, imputation methods will be used to estimate the overall impact of missing data on outcomes. Administrative data from the Institute of Clinical and Evaluative will be used for the purposes of evaluating the primary outcome, and comparing the impact of missing data on outcomes.

*Economic Evaluation Plan*

The objective of the economic evaluation is to compare the cost-effectiveness of the CATCH-ED intervention with usual care, using patient-level data from the randomized clinical trial and linked administrative data at the Institute for Clinical Evaluative Sciences (ICES), Toronto. The Ontario MOHLTC perspective will be used in the analysis. In Ontario, the Ministry pays for physician visits, laboratory tests, imaging, hospitalization, emergency department visits, same day surgery/ procedure, complex continuing care and some home care services. In addition, the Ministry pays for prescription drugs for those older than 65 years old, live in a Long-Term Care Home or a Home for Special Care or enrolled in special programs such as the Ontario Disability Support Plan (ODSP). The time horizon for the economic evaluation will be 12 months (maximum follow-up of the trial).

The primary outcome will be the incremental cost per quality-adjusted life-year (QALY) gained though the intervention compared with usual care. The secondary outcomes include the incremental cost per ED visit avoided and incremental cost per hospital-day avoided.

Measuring QALYs: A QALY is a year of life experienced with a particular health-related quality of life (HRQoL) or health state utility, as represented on a scale from 0 to 1, where 0=death and 1=full health. The EQ-5D and SF-6D (converted from SF-12), generic preference-based instruments that have been used in mental health patients, will be used to assess patients’ health state utility at baseline, 6 months and 1 year. We will calculate each patient’s QALY from the utility scores using the area-under-the-curve approach, with linear interpolation between assessment points (Figure 1).

[figure not shown]

QALY0-90 days

QALY6 -12 months

QALY0-6 months

Figure 1. Calculating QALYs from EQ-5D utility scores

Measuring resource use and costs: We will obtain the health care costs of each patient from linked administrative data at ICES (Table 1). Informed consent will be collected from each participant for linking study data to the administrative data at ICES. The two dataset will be linked using patients’ OHIP numbers.

Table 1. Data source

| **Resources** | **Sources** | **Variables** |
| --- | --- | --- |
| Hospitalization | Discharge Abstract Database | Cost estimated using Resource Intensity Weight (RIW) and cost per weighted case |
| Outpatient laboratory / imaging services and physician services (including inpatient, office and undefined service) | Ontario Health Insurance Plan (OHIP) Claims Database | OHIP billing cost estimated using utilization frequency of each service and cost per visit from OHIP fee schedule |
| Emergency Room visits / Same Day Surgery or procedure | National Ambulatory Care Reporting System (NACRS) and Same Day Surgery | Cost estimated using RIW and cost per weighted case |
| Outpatient prescription drugs | Ontario Drug Benefit Plan (ODB) | Drug cost and dispensing fee |
| Home care services | Home Care Database | Utilization frequency for each type of home care service |
| Complex continuing care | Continuing Care Reporting System | Case-mix index and duration between events or RWPD |

RWPD: RUG Weighted Patient Day is calculated by multiplying the case-mix index (CMI) and number of days for a particular RUG event. It accounts for admissions, assessments, re-entries, discharges, etc.

Calculating incremental cost per QALY gained: We will estimate average and incremental costs and QALYs for each group using multiple regressions:

[figure not shown]

[figure not shown]

where x is a vector of patient characteristics (e.g., age, sex), U­0 is the utility at baseline,10 TX­ is a treatment variable (TX=1 for intervention group), and the regression estimates β1 is the incremental cost and α1 is the incremental QALY.

Calculating incremental cost per ED visit avoided: We will estimate average and incremental costs (excluding ED visit costs) for each group using multiple regressions. The incremental cost per ED visit avoided is the incremental cost divided by the incremental number of ED presentations (more details in the statistical analysis section).

Calculating incremental cost per hospital-day avoided: We will estimate average and incremental costs (excluding hospitalization costs) for each group using multiple regressions. The incremental cost per hospital-day avoided is the incremental cost divided by the average number of hospital-days (more details in the statistical analysis section).

Calculating net benefit regression: A treatment is cost-effective if the ICER is less than what the decision maker is willing to pay (λ) for the extra benefit (QALY gained, ED visit avoided or hospital-day avoided):

∆C/∆E <λ

We can also express this decision in terms of incremental net benefit, ∆NB:

∆NB = λ ∆E - ∆C

A treatment is cost-effective if it has a positive ∆NB, the value of the intervention’s extra benefits outweighs its extra costs. It is easier to estimate confidence interval for ∆NB because it is not a ratio. We will estimate the incremental net benefit of the intervention (β1) using multiple regressions:

NB= β0 + β1TX + β**X**

We could identify subgroups for whom the intervention is especially cost-effective using interaction terms. We will conduct net benefit regression analysis using different values of λ and will represent uncertainty using cost-effectiveness acceptability curves.

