**Implementation**

In February, 2012, the Alliance, a collaborative of 7 TC LHIN teaching hospitals, implemented CATCH-ED at 3 TC-LHIN Hospitals, in partnership with 4 CHCs and 6 Community Mental Health Agencies, targeting frequent ED users (>5 visits in the previous 12 months). An implementation evaluation is currently underway to assess challenges and facilitators of implementation at each site, fidelity of the intervention to the program model and stakeholder and consumer perspectives on the intervention for the purposes of further program development / adaptation. Implementation evaluation will be followed by an outcome evaluation, using a randomized controlled design. CATCH-ED is currently supported by the Alliance, the TC-LHIN, the Ontario MOHLTC and BRIDGES (Building Bridges to Integrated Care, Department of Family and Community Medicine, University of Toronto). The Alliance facilitates program partner meetings and implementation of the intervention. The TC-LHIN has provided funding to the CHCs to increase capacity for frequent users and trauma-informed services / counseling. A senior TC-LHIN manager participates in the Frequent Users Advisory Committee chaired by the Alliance. BRIDGES is providing funding for the implementation and outcome evaluation, with an anticipated time of completion of March 31st, 2014. BRIDGES, in addition, provides infrastructure and support for data collection and a cost-effectiveness evaluation of the program through the Applied Health Research Centre (AHRC) at the Li Ka Shing Knowledge Institute, St. Michael’s Hospital. The Ontario MOHLTC has provided start up funding for the implementation evaluation and will be participating in further discussion on expansion of the program to other sites in Ontario.

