**Methods - Outcome Evaluation**

The study design is a randomized controlled trial in which multiple longitudinal outcome measures will be collected on both the intervention and control groups to assess client characteristics and selected outcomes of interest.

Frequent users will be recruited to the study over a 9-month period and followed for 12 months. Program participants will complete survey interviews at baseline, 6 and 12 months to assess health status, mental health, substance use, self reported acute care service use, service satisfaction and their working alliance with their primary clinician. Self-reported acute care use will be complemented by administrative data linkage to examine acute care service use 12 months prior and 12 months following referral to the intervention. Participants will also complete survey interviews at 3 and 9 months to assess their service use and to confirm their contact information and any time spent outside the Province during the previous three-month period.

*Sample Size Calculation*

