In determining a sample size calculation, three important factors were considered: 1) participants are eligible by being at the extreme of the distribution of emergency visits in the overall population and hence regression to the mean may play an important role in any observed change over time, 2) accessing emergency services may in fact provide a treatment that may contribute to change over time in an 'untreated' group, 3) previous studies have found that emergency visits tend to follow a negative binomial distribution (a count distribution with highly right skewed data), and 4) a proportional reduction in the rate of emergency department visits is the desired primary measure of impact of this intervention. To account for these factors, published data of Shumway et. al. (2008) was used to estimate the distribution of emergency department (ED) visits in an untreated group and its natural reduction over time; their study of frequent ED users (>5 visits/year) included a ‘usual care’ group and reported the mean and standard deviation of ED visits over 2 years of follow-up in 6 month blocks. The sample size calculation was performed using the formula derived by Toshiro Tango (Statistics and Probability Letters 79 (2009) 466-472) which uses a Poisson type outcome and assumes a random effect for each individual, which can accommodate a negative binomial or other more dispersed distribution. This approach also takes into account any fixed effects that covariates may have in both the pre and post-intervention period. Ultimately, this sample size calculation proposes that a sample size of 64 in each arm would allow the detection of a 20% reduction in ED visit rates (the minimum clinically significant difference we would like to be able to demonstrate). Since up to 30% attrition is expected, among participants, the final sample size will be 166 participants, 83 in each arm.

*Randomization process*

Participants will be recruited among successive referrals from participating TC-LHIN Hospitals. Participants able to provide capable informed consent will be invited to participate to the study. A research coordinator or research assistant will obtain written informed consent and complete a baseline interview prior to randomization to CATCH-ED vs. treatment as usual. Randomization will be allocated through the web-based electronic case report forms (eCRFs.) The randomization sequence will be generated by random computerized sequence in variable block sizes.

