**Data Collection Plan and Data Management**

The Data Coordination Centre (DCC) will be the Applied Health Research Centre (AHRC), an academic research organization based at St Michael's Hospital. AHRC will use software called Medidata RAVE ([www.mdsol.com](http://www.mdsol.com/)) to create the web-based electronic CRF (eCRF). All study data will be securely stored on local servers at St Michael’s Hospital throughout the duration of the study and for up to 10 years after the study is complete. All study subjects will be identified in the database by a unique study ID number. Linkages between the patient name/contact information and the study ID will be retained at the local site and not shared with the study DCC or outside the institution. At the end of the study (after all analyses are complete) the DCC will transfer all study datasets over to the study PI. Data will only be accessible by authorized study site personnel and authorized central DCC personnel. Authorized personnel receive a username and password which is unique, and database access is controlled by the DCC in collaboration with the Principal Investigator.

Three members of this research team ([name]) are Toronto site principal investigators of the At Home / Chez Soi Research Demonstration Project on Homelessness and Mental Health, a large longitudinal national program evaluation funded by the Mental Health Commission of Canada. This proposed study will utilize data collection instruments and knowledge gained from the At Home / Chez Soi study to help engage and follow frequent users of the ED. Survey interviews will be completed by research assistants (RA). The RAs, supported by a Research Coordinator (RC), will be responsible for recruiting study participants, collecting data from CATCH-ED participant clinical records to ascertain clinical diagnoses and frequency of contact with CATCH ED clinicians and administering participant survey interviews at entry point into the program and at 3, 6, 9 and 12 months following enrolment. RAs will be updating the tracking information at all participant interviews and at monthly intervals through telephone follow up with each participant. A brief summary of client measures is provided below.

*Socio-demographic variables*: Research staff will collect the following information: basic demographic information, residential status, income support status.

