*Colorado Symptom Index (CSI):* The CSI was designed specifically for individuals with mental health problems. It is a 14-item instrument which assesses the presence and frequency of symptoms of mental illness experienced within the past month. Responses are provided using a 5-point Likert scale with answer choices ranging from 0 (not at all) to 4 (at least every day). A higher score indicates a higher level of symptoms. The Colorado Symptom Index is a widely used tool in research as a self-report measure of psychiatric symptomatology. The CSI has been reported to have excellent internal consistency (.92) and test-retest reliability (.71). Evidence of the CSI’s validity is strong as CSI scores have been proven to distinguish between individuals with and without mental health service needs and were significantly correlated with functioning(Boothroyd and Chen, 2008).

*ASI:* The alcohol and drug module of the Addiction Severity Index (ASI), the most widely used instrument in the field, will be utilized. The ASI is a structured interview instrument that yields information about the severity of lifetime and recent (previous 30 days) drug and alcohol use (McLellan et al, 1980). Five indices will be used to measure substance abuse-the number of days that alcohol or substances were abused in the past month, the amount of money spent on alcohol or drugs in the past month, and the participants’ rating of the need for alcohol or drug use treatment. The ASI has good inter-rater and test-retest reliability and good concurrent and discriminant validity. It has been used extensively with the homeless population (Hwang et al, 2005).

*Participant Service Use:* Service use events will be tracked using both self-reported and administrative data. We will establish the number of hospitalizations, days in hospital and emergency department visits during the year prior to program enrolment as well as the 12 month follow-up period. We will also collect data on non-acute service use, such as mental health, substance use, and primary care visits, using service use forms adapted from the At Home / Chez Soi project on homelessness and mental health.

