*Service satisfaction – SSS10:* This scale is a shorter version of the SSS-30 (Greenfield & Attkisson, 2004) which was extensively tested in Alberta and in a few services in British Columbia (Adair et al, 2005). Participants will be asked whether they had received any assistance with an array of different care needs. The three needs categories will include: coordination of services; family and social networks and community linkages; and life skills training, support and practical needs assistance.

*Working Alliance Inventory-Participant (WAI-PAR):* This 12-item self-report measure (modified from the original 36 item version) is designed to assess the working-alliance construct based on the theory that a working alliance common to all therapeutic relationships grows out of client-therapist agreement on therapy goals, agreement on therapy tasks, and development of a strong relational bond between client and therapist (Busseri et al, 2003). There are 4 items (chosen from the longer scale using factor analysis) in each of three subscales: task, goal and bond. Items are rated on 7-point scales (1=never, 7=always). Ratings yield task, goal and bond subscale scores as well as an average score based on all items. The scale has good psychometric properties, with mean reliability estimates ranging from .79 to .97, with a modal estimate of .92 (Horvath & Greenberge, 1989; Hanson et al, 2002).

*Administrative Data Linkage*

Data linkage will be conducted at the Institute for Clinical Evaluative Sciences (ICES) where population based health information is available, at the patient level, for all Ontarians using formal health services. Subjects will be linked deterministically using their Ontario Health Card Number (encrypted at ICES to preserve anonymity). Health administrative data will be used to identify individuals’ use of hospital and physician services in a 12-month observation window preceding and following their enrolment to the CATCH-ED program. Health service use will be examined by the National Ambulatory Reporting System (NACRS), the Discharge Abstract Database (DAD), the Ontario Mental Health Reporting System (OMHRS) and the Ontario Health Insurance plan (OHIP) for ED visits, outpatient clinics and inpatient hospitalizations.

*Other Administrative Data*

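### A per-protocol set based on programme contact would exclude people from the CATCH-ED arm only; an adherence analysis that keeps everyone randomised would be safer

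*Protocol*

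**What the plan says.** The Analysis Plan commits every outcome to two analyses: "All analyses will use an intent-to-treat perspective and will be compared with a per-protocol analysis". It does not say who belongs to the per-protocol set.

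The Data Collection Plan gives one source for programme contact. Research assistants are responsible for "collecting data from CATCH-ED participant clinical records to ascertain clinical diagnoses and frequency of contact with CATCH ED clinicians".

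Under Randomization process, participants "complete a baseline interview prior to randomization to CATCH-ED vs. treatment as usual". No content is laid down for usual care against which a control's adherence could be judged.

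Other data could bear on who received what. The Methods section says that "multiple longitudinal outcome measures will be collected on both the intervention and control groups" and that "Participants will also complete survey interviews at 3 and 9 months to assess their service use". The Data Collection Plan adds: "We will also collect data on non-acute service use, such as mental health, substance use, and primary care visits". For the service satisfaction scale, "Participants will be asked whether they had received any assistance with an array of different care needs". None of these is restricted to one arm, and none is described as asking about CATCH-ED contact.

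On access to the programme, the Implementation section describes a service already operating at three hospitals and "targeting frequent ED users (>5 visits in the previous 12 months"), which is also the trial's population.

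**The concern.** A per-protocol analysis is usually read as the effect in those who took up the treatment. Here, take-up can be judged in one arm only. A CATCH-ED participant who never engages can be excluded. The control who would not have engaged either cannot be recognised, and stays. What remains is a selected intervention group set against an unselected control group.

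The Background describes this population as hard to engage, so non-engagement should be expected, and it may well be related to the course of ED use. A favourable per-protocol result beside a null intent-to-treat result could then be taken as evidence that the programme works in those who engage, when selection alone might produce it. The reverse error is equally possible.

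Contamination in the other direction also matters. A control who receives CATCH-ED and is not identified would count as an adherent control and would dilute the intent-to-treat contrast. The protocol describes no check for this.

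**Working it through.** The protocol states no figure for engagement, crossover or the per-protocol effect, so there is nothing to reproduce. The check has three parts.

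**1. Can a contact-based rule be applied to both arms?** Contact frequency is abstracted from programme records. A control has such a record only after entering the programme. Usual care has no engagement standard. So a minimum-contact rule can remove people from the CATCH-ED arm, and it has no counterpart among controls. A more precise rule in a statistical analysis plan would not change that.

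**2. How large could the bias be?** The primary outcome is a proportional change in ED visit rate from before to after the intervention, so the calculation must be on that scale.

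- Let g be the post/pre rate ratio in engagers and g·r the ratio in non-engagers. Thus r is a ratio of proportional changes, not of visit levels.
- Let p be the share of the arm's pre-period visits made by non-engagers. If baseline rates are equal, p is simply the share of participants.
- With no true effect, both full arms change by g·[(1−p) + p·r].
- After non-engagers are removed from the CATCH-ED arm only, that arm changes by g.
- Apparent rate ratio = 1 / [(1−p) + p·r].

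Both p and r are assumptions:

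| p | r | Calculation | Apparent rate ratio |
|---|---|---|---|
| any | 1 | 1/1 | 1.00 |
| 15% | 1.5 | 1/1.075 | 0.93 |
| 25% | 1.5 | 1/1.125 | 0.89 |
| 30% | 2 | 1/1.30 | 0.77 |
| 25% | 0.5 | 1/0.875 | 1.14 |

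To produce a spurious 20% reduction, the difference the Sample Size Calculation calls the minimum clinically significant one, r must equal (1/0.8 − 1 + p)/p. That is 0.45/0.20 = 2.25 at p = 20%, and 0.55/0.30 = 1.83 at p = 30%.

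The first row matters. If non-engagers visit more often than engagers by the same factor before and after, then r = 1 and there is no bias, however many are excluded.

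**3. What would control crossover do?** Suppose the true rate ratio is 0.8 and a fraction c of controls receives the full benefit throughout follow-up. The observed ratio is 0.8/(1 − 0.2c). At c = 10% it is 0.8/0.98 = 0.816, an 18.4% reduction. At c = 20% it is 0.8/0.96 = 0.833, a 16.7% reduction. These values of c are assumptions too.

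**The case against.** The strongest reply is that the protocol does not define the per-protocol set, and that such definitions are commonly left to a statistical analysis plan, which is not shown. The set might rest on eligibility or consent and then apply equally to both arms. This stands to a point: the missing definition is no error, and the concern is conditional on a contact-based set. But contact is the one adherence measure the protocol names, and no wording of a contact rule makes it two-sided.

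A reader might infer that control crossover is invisible. The documents do not support that. The service-use interviews and forms, the satisfaction scale and the working alliance measure are not limited to one arm, and a control who entered the programme would have a programme record. Nor is the term for the people whose records are abstracted expressly confined to the intervention arm. What stands is narrower: no step to look for such controls is described. The crossover route is itself inferred, since the protocol neither allows nor bars later referral of controls, and the assumed rates give modest dilution.

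A reader might also infer a spurious effect of 23% from the 0.77 above. That is an illustration at one assumed pair of values. It does not follow from non-engagers merely having twice the ED visits, because a stable difference in level cancels in a pre/post change.

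Finally, intent-to-treat is the stated perspective, and a per-protocol analysis beside it is common practice. This is right, and it limits the point to a secondary analysis.

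**Conclusion.** The point holds in a limited form. A per-protocol set based on programme contact would break the randomised comparison in one arm only, and a later definition of contact would not cure that. The resulting bias can go either way. It exists only if proportional change in ED use differs between non-engagers and engagers. Its size is unknown: the range of 0.77 to 1.14 rests wholly on assumed values of p and r.

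On crossover, the supported statement is that the protocol plans no step to identify or record controls who receive CATCH-ED, although its data could partly reveal them.

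It would be wrong to conclude that the trial's main result is compromised. The one-arm exclusion does not touch the intent-to-treat estimate. Crossover, if it occurs, would move that estimate towards no effect but would not invalidate it. This is a cheap improvement to a secondary analysis.

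**What to change.** Four changes to the Analysis Plan and Data Collection Plan:

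1. State that conclusions rest on the intent-to-treat analysis.
2. Use a CACE estimate, with randomised arm as the instrument and all randomised participants kept, either in place of the per-protocol analysis or as the preferred adherence analysis beside it.
3. Define before analysis what counts as having received CATCH-ED.
4. Check CATCH-ED client records for participants in both arms over the 12 months, and record any contact by controls.

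The cost is some wording, one additional model and one record look-up per control (83 at the planned sample size) in a source the research assistants already abstract. The statistical price is a wider interval than a per-protocol analysis would give. CACE also relies on the exclusion restriction: allocation may affect ED use only through programme receipt as defined, so contact below the receipt threshold must be assumed to have no effect. That assumption should be stated with the result.
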